The changes in the cold and hot patterns for participants will be measured using a cold-heat pattern identification questionnaire at baseline and 8 weeks post-treatment. The cold-heat pattern identification questionnaire was developed by the Korea Institute of Oriental Medicine (KIOM) and is a self-report questionnaire consisting of eight items related to cold patterns and seven items related to hot patterns [24]. The reliability and validity of the questionnaire have been confirmed [25]. As an exploratory outcome measure, fecal samples of participants before and after taking the investigational product (baseline and 8 weeks post-treatment) will be examined to identify changes in the gut microbiome through next-generation sequencing. The time points for each outcome measure are presented in detail in Table 1.

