### Sample size

This is the first study to explore the feasibility and lipid-improving effect and safety of HHT granules compared with placebo granules. Therefore, a formal sample size calculation is not required [26]. Based on a study recommending a minimum of 12 participants per group for a pilot study [27], we selected 15 participants per group as a sample size for this trial, considering a 20% dropout rate.

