### Statistical analysis

An independent statistician will conduct statistical analysis using SAS® Version 9.4 (SAS Institute Inc., Cary, NC). In principle, efficacy analysis will be conducted using a full analysis set according to the intention-to-treatment principle, including all randomly assigned participants receiving at least one evaluation after the investigational product has been prescribed at least once. If necessary, per protocol set (PPS) analysis will also be conducted including only participants who have completed the entire process as described in the protocol and have no significant violations. Participants less than 70% compliant with the investigational product will be excluded from the PPS analysis. Safety analysis will include all data obtained from participants who have taken at least one investigational product.

The demographic and general clinical characteristics of participants will be summarized by group. Continuous data will be presented as mean and 95% confidence intervals or median according to the distribution of the data and dichotomous data as frequency and percentage. Continuous data will be analyzed using the independent *t* test or Wilcoxon rank sum test, and dichotomous data will be analyzed using the chi-square test or Fisher’s exact test.

The primary outcome in this study is the mean change in LDL-C from baseline to week 8. A two-sided test with a significance level of 5% will be performed using an analysis of covariance with baseline as the covariate and the treatment group as the fixed factors. The intra-group changes of outcome measures from baseline to post-treatment will be analyzed using paired *t* test or Wilcoxon signed rank test for continuous variables and the chi-square test or Fisher’s exact test for dichotomous variables. Furthermore, repeated measures analysis of variance will be used to compare the differences in trends between visits in each group. Missing values will be replaced with the multiple imputation method. If necessary, a subgroup analysis can be performed by categorizing the participant’s initial characteristics at the screening or baseline visit.

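### Within-group change in dichotomous variables is assigned the chi-square or Fisher's exact test, which ignore the pairing; the clause should name McNemar's test (minor correction)

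*Protocol article*

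**What the plan says.** The Statistical analysis section of the protocol article names tests for dichotomous data in two places.

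- **Between groups.** In the paragraph that names the independent t test and the rank sum test for continuous data, "dichotomous data will be analyzed using the chi-square test or Fisher’s exact test". The groups are independent, so this is appropriate.
- **Within groups.** The next paragraph gives a single rule for before-after change in each group. Continuous variables get a test for pairs, either parametric or rank-based. The sentence then ends by adding the dichotomous ones: "signed rank test for continuous variables and the chi-square test or Fisher’s exact test for dichotomous variables".

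No McNemar test or other paired method for binary data appears anywhere in the article.

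The primary analysis is separate: "The primary outcome in this study is the mean change in LDL-C from baseline to week 8", analysed by covariance analysis with baseline as the covariate.

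**The concern.** The within-group sentence respects pairing for continuous variables and drops it for dichotomous ones. It reuses the two tests that the previous paragraph correctly assigns to independent groups.

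A chi-square or Fisher test can be run on such data in two ways, and neither tests within-person change correctly.

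- **Time point by status.** The baseline and later answers of 15 people are treated as the answers of 30 different people. The variance is wrong, and positive within-person correlation makes the test conservative.
- **Baseline status by later status.** The test asks whether the two answers are associated. That is usually true of repeated measurements and says nothing about change.

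At stake are p-values for any secondary or safety variable that is later dichotomised and compared before and after within a group. Examples would be a laboratory value classed as normal or abnormal, or a pattern classed as present or absent from the instrument "measured using a cold-heat pattern identification questionnaire at baseline and 8 weeks post-treatment". Because the article names a test, this is a wrongly stated rule and not a detail left to an analysis plan.

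**Working it through.** **Inputs from the article.** The Sample size section starts from a published recommendation ("Based on a study recommending a minimum of 12 participants per group for a pilot study") and continues: "we selected 15 participants per group as a sample size for this trial, considering a 20% dropout rate". This reproduces: 12 / (1 − 0.20) = 15. Two-sided 5% is stated for the primary analysis ("A two-sided test with a significance level of 5% will be performed using an analysis of covariance") and is assumed here for the within-group tests.

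**Assumed inputs.** The article gives no proportions or within-person correlations for dichotomous variables, so all of those below are assumptions.

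**Notation.** Of n pairs, *a* are positive at both times, *b* change from positive to negative, *c* change from negative to positive, and *d* are negative at both times. Change depends on *b* and *c*. Exact McNemar: p = 2 × P(X ≤ min(b, c)), with X ~ Binomial(b + c, 0.5). Mid-p subtracts P(X = min(b, c)) from that.

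**Step 1, one table, time point by status.** Let n = 15, with 9 positive before, 3 after, and all six changers in the same direction (a = 3, b = 6, c = 0, d = 6).

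- Fisher on 9/15 against 3/15: p = 0.060
- Chi-square on the same margins: p = 0.025
- Exact McNemar: 2 × 0.5^6 = 0.031
- Mid-p McNemar: 0.03125 − 0.5^6 = 0.016

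**Step 2, one table, cross-classified.** Let 7 be positive at both times, 8 negative at both times, and nobody change. Fisher gives 1 / C(15, 7) = 1/6435 = 0.0002. McNemar gives p = 1.

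**Step 3, why the first reading is conservative.** With equal true proportions p, the paired difference has variance (2p(1 − p)/n)(1 − ρ), where ρ is the within-person correlation. The independent-sample formula leaves out (1 − ρ). The large-sample Type I error at ρ = 0.5 is therefore 2 × (1 − Φ(1.96/√0.5)) = 0.0056.

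**Step 4, exact Type I error.** All tables of 15 pairs were enumerated with multinomial probabilities. With cov = ρ√(p1(1 − p1)p2(1 − p2)), the cell probabilities are p1·p2 + cov for *a*, p1 minus that for *b*, p2 minus that for *c*, and the remainder for *d*. True proportion 0.5 at both times:

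| Test | ρ = 0 | ρ = 0.3 | ρ = 0.5 | ρ = 0.7 |
|---|---|---|---|---|
| Chi-square | 4.6% | 1.8% | 0.6% | 0.1% |
| Fisher | 1.7% | 0.5% | 0.1% | <0.1% |
| Exact McNemar | 1.8% | 1.0% | 0.4% | <0.1% |
| Mid-p McNemar | 3.9% | 2.8% | 1.5% | 0.3% |
| Asymptotic McNemar | 4.4% | 5.0% | 4.3% | 1.8% |

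The chi-square entry at ρ = 0.5 agrees with step 3.

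**Step 5, exact power.** Same enumeration, n = 15:

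| Test | 70% to 30%, ρ = 0.3 | 80% to 40%, ρ = 0.4 |
|---|---|---|
| Fisher | 41% | 42% |
| Chi-square | 61% | 65% |
| Exact McNemar | 54% | 59% |
| Mid-p McNemar | 69% | 78% |
| Asymptotic McNemar | 75% | 90% |

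**Step 6, after the planned dropout.** With 12 pairs and 80% to 40% at ρ = 0.4, power is 35% for Fisher, 57% for chi-square, 33% for exact McNemar, 56% for mid-p and 77% for asymptotic McNemar. At that size neither exact nor mid-p McNemar beats chi-square.

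**The case against.** The strongest reply is that the rule may never be used. LDL-C change is continuous. The listed secondary outcomes are laboratory values, vascular and body measurements, blood pressure and questionnaire results, none stated as dichotomous. The safety laboratory tests are compared before and after in each group, but no normal/abnormal classification is mentioned. The cold-heat questionnaire is described by its items, without a cut-off. Adverse events and the blinding question are categorical, but they are not baseline-to-post-treatment pairs. All of this stands and limits the point to derived variables.

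Three stronger readings are tempting, and the documents do not support them.

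- **That the trial's efficacy result is compromised.** It rests on the randomised comparison of LDL-C, which this clause does not touch. The within-group tests are supplementary in a 30-person pilot.
- **That the plan will declare change where nobody changed.** The p = 0.0002 in step 2 needs the cross-classified reading. The article does not specify that table, and its wording about change does not suggest it. Under the other reading, with positive correlation, the error is conservative.
- **That McNemar's test guarantees more power or restores the 5% level.** Chi-square is one of the two planned tests. With 15 pairs its power exceeds that of exact McNemar (61% against 54%), and in step 1 it gives the smaller p-value (0.025 against 0.031). Exact McNemar's own Type I error at ρ = 0.5 is 0.4%, below chi-square's 0.6%. Much of the conservatism is small-sample discreteness, which the exact paired test does not cure.

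The reply does not rescue the clause. It prescribes an independent-samples test for paired data, in a sentence that handles the pairing correctly for continuous variables.

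**Conclusion.** The point holds as a minor correction. The clause is wrong as written: for paired dichotomous data, chi-square and Fisher either ignore the pairing or answer a different question. The argument rests on testing the right hypothesis with the pairing respected, not on a promised gain in power.

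The numerical size depends on assumed proportions, correlations and 15 complete pairs. In the cases examined at n = 15, mid-p McNemar has more power than either planned test and stays below 5% Type I error. Its advantage over chi-square is gone at 12 pairs. The correction would matter only if a secondary or safety variable is dichotomised and compared before and after within a group.

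**What to change.** Replace the dichotomous part of the within-group sentence with wording such as:

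> Within-group change in dichotomous variables from baseline to post-treatment will be analysed with McNemar's test (mid-p version) and reported as the paired difference in proportions, (b − c)/n, with a 95% confidence interval.

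Mid-p is preferred at about 15 pairs because exact McNemar is itself conservative there. Keep the chi-square or Fisher's exact test for between-group comparisons only; that part of the plan needs no change.

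The cost is one clause. Data collection, the sample size and the primary analysis stay as they are.

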### Data monitoring

We will use a web-based electronic CRF developed by Medidata (NY, USA) for data collection and verification. It will be managed by data management team from KIOM. The electronic CRF is accessible only to investigators who are directly involved in the clinical trial and received the relevant education. To ensure the data quality, the range of data values will be set in advance. Although data entry will be performed only once by the investigators, data quality will be managed with two verification processes for each clinical research associate and data manager. A clinical research associate at KIOM ([name]), a supporting institution, will visit the hospital regularly to monitor protocol violations, recruitment rate, document reporting, and adverse events (including serious adverse events) during the study period. The detected item will be properly resolved through discussions with investigators. No formal data monitoring committee will be convened. There is currently no planned auditing. However, auditing can be conducted to preserve the integrity of the trial by the quality assurance team at the supporting institution, independent from the investigators.

### Patient and public involvement

This study is designed to explore the feasibility and preliminary effectiveness and safety of HHT for patients with hyperlipidemia. HHT is an herbal drug approved as a generic drug by the Korea Ministry of Food and Drug Safety in the Republic of Korea and is easily accepted by patients. Using HHT for hyperlipidemia may improve blood lipid levels, preventing cardiovascular disease and improving the quality of life. In addition, the outcome measures used in this trial are considered important endpoints for patients with hyperlipidemia in clinical practice. However, patients were not involved directly in developing the study design and will not be involved in the recruitment or conduct of the study. In addition, there is no plan to communicate the results of this study to trial participants. If the participants request the results of the study after the clinical trial has been completed, we will provide a summary of the results.

### Ethics and dissemination

The trial protocol has been approved by the Korea Ministry of Food and Drug Safety (approval number: 32578) and the IRB of Daejeon Korean Medicine Hospital of Daejeon University (approval number: DJDSKH-19-DR-18). The study was registered at the Clinical Research Information Service (CRIS) (registration number: KCT0004564). Any modifications to the protocol will be reapproved by the IRB prior to implementation and documented in CRIS. All participants will receive a detailed description of the research process from a licensed Korean medicine doctor and be asked to sign an informed consent form prior to participation. In addition, consent forms for the use of human biological materials will be acquired for the handing of fecal samples from the participants. The results of this study will be submitted for publication in peer-reviewed journals and can be disseminated through conference presentations.

## Discussion

This is a study protocol for a randomized, double-blind, placebo-controlled, parallel, investigator-initiated, pilot clinical trial evaluating the effect of HHT on patients with hyperlipidemia. We will evaluate the preliminary efficacy and safety of 8-week administration of HHT compared with placebo granules and assess the feasibility of large-scale RCTs. According to the 2019 European Society of Cardiology and European Atherosclerosis Society Guidelines for the management of dyslipidemias, LDL-C analysis is recommended as the primary lipid analysis method for screening, diagnosis, and management [28]. Therefore, we set the inclusion criteria and primary outcome measure for our study as LDL-C, not TC or TG. In addition, we set 250 mg/dl as the upper bound for LDL-C in the inclusion criteria by referencing the guidelines for clinical trials for hyperlipidemia treatment by the Korean Ministry of Food and Drug Safety [29], considering that this study will include participants who are not taking conventional lipid-lowering drugs. According to a consensus document on clinical research in Chinese medicine, it is recommended to recruit participants according to the conventional medicinal diagnosis, and then to perform pattern identification before randomization. Recruiting participants based on pattern identification can be considered if a limited number of identifiable patterns exist [30]. To the best of our knowledge, there has been no consensus on standardized pattern identification for hyperlipidemia. Therefore, we will recruit hyperlipidemia participants according to the conventional medical diagnosis, and then perform cold-heat pattern identification before randomization.

Although there is a previously published clinical trial evaluating the efficacy and safety of HHT in hyperlipidemia, it directly compared HHT and Simvastatin, and the duration of treatment was 4 weeks [15]. Our study attempts to evaluate the efficacy of HHT compared to placebo in patients with hyperlipidemia who are not taking conventional lipid-lowering drugs such as statins, and the treatment period was set to 8 weeks. Therefore, there was no reference to calculate the formal sample size, and if this pilot study design is feasible, a confirmatory clinical trial will be conducted by calculating the appropriate sample size based on the results of this study.

Herbal medicine contains multiple active components that act on multiple targets and has the potential to overcome the limitations of conventional medications with a single active constituent [31]. According to an RCT comparing HHT with statin in patients with hyperlipidemia, there was no statistically significant difference in blood lipid parameters between the two groups, but fasting blood glucose was significantly lower in the HHT group than in the statin group [15]. In addition, comparison of the administration of HHT plus statin and statin alone to patients with both hypertension and hyperlipidemia showed a significant improvement in inflammatory factors in favor of HHT plus statin [16]. Furthermore, when HHT was administered to obese patients, body weight, body fat, and waist circumference decreased significantly [32]. The results of these studies suggest the efficacy of HHT as a single treatment for metabolic syndrome, which is a complex lifestyle disease including hyperlipidemia, glucose metabolism abnormalities, hypertension, and obesity. Therefore, we set blood glucose parameters, blood pressure, and anthropometric parameters as the secondary outcome measures.

Although hyperlipidemia itself is asymptomatic, it is the most important risk factor for atherosclerosis, the major cause of cardiovascular disease [33]. Studies have suggested that non-invasive measurements of baPWV and ABI might be used as markers of atherosclerosis [34, 35]. In addition, hs-CRP, fibrinogen, and homocysteine have been suggested as biomarkers of atherosclerosis [36–38]. Therefore, we will measure baPWV, ABI, hs-CRP, fibrinogen, and homocysteine as markers of atherosclerosis to investigate the effect of HHT on atherosclerosis.

In EATMs, HHT is a representative heat-clearing medicine and its effect on alleviating fever in animal models has been demonstrated [39]. Therefore, we will examine the changes in cold and hot patterns in participants using a validated cold-heat pattern identification questionnaire after 8-weeks of HHT administration.

Recent studies have shown a close relationship between hyperlipidemia and gut microorganisms and patients with hyperlipidemia often exhibit intestinal microbiota disorders that might further impair lipid metabolism [40]. Recent research showed that *Berberine*, the main component of *Coptidis Rhizoma,* improves lipid metabolism in the liver by changing gut microbiota and by regulating bile acid metabolism and the farnesoid X receptor pathway in the intestine [41]. Therefore, we will investigate the changes in the gut microbiome before and after HHT administration and explore the effects of HHT on the composition, diversity, and species abundance of gut microorganisms in patients with hyperlipidemia.

Side effects from the use of HHT may include gastrointestinal reactions such as anorexia, stomach discomfort, nausea, and vomiting, and hypersensitivity reactions such as rash and urticaria. In rare cases, interstitial pneumonia or liver dysfunction may occur. However, according to related clinical trials in which HHT was administered to patients with hyperlipidemia, no serious adverse reactions were observed and no abnormalities were found in blood and urine tests and electrocardiograms [15, 42].

In our study, there is a limitation due to the small sample size of 15 participants per group and this may not be enough to draw a definite conclusion of the efficacy of intervention. However, to the best of our knowledge, this is the first RCT assessing the effect of HHT on patients with hyperlipidemia. If the treatment effect and safety of HHT compared with placebo granules is found to be promising in this study and the study design is feasible, we will design a confirmatory, large-scale RCT based on the results of the study to draw definitive conclusions regarding the efficacy of HHT.

In conclusion, this article presents the protocol for a rigorously well-designed, double-blind, placebo-controlled, pilot RCT on HHT for patients with hyperlipidemia. Our study has the strengths of using placebo granules as the control and using the objective blood lipid parameter, LDL-C, as the primary outcome, to minimize performance bias and detection bias. The findings of this study are expected to provide a base for large-scale, confirmatory RCT to confirm the efficacy and safety of HHT for the treatment of patients with hyperlipidemia. Additionally, stronger evidence of HHT as a treatment option for hyperlipidemia may be provided to clinicians, patients, and researchers.

### Trial status

This trial has not started participant recruitment yet. Protocol version number and date: version 1.2 (December 6, 2019). Date recruitment will begin: January 15, 2020. Approximate date when recruitment will be completed: December 31, 2020.

## Data Availability

The datasets used or analyzed (or both) during the current study are available from the corresponding author on reasonable request.

## Abbreviations

ABI: Ankle-brachial index
ALT: Alanine aminotransferase
Apo: Apolipoprotein
AST: Aspartate aminotransferase
baPWV: Brachial-ankle pulse wave velocity
CONSORT: Consolidated Standards of Reporting Trials
CRF: Case report form
CRIS: Clinical Research Information Service
EATM: East Asian traditional medicine
EQ-5D-5L: Five-level EuroQol-5 dimensions
HDL-C: High-density lipoprotein cholesterol
HHT: Hwangryunhaedok-tang
HMG-CoA: 3-Hydroxy-3-methyl-glutaryl-coenzyme A
hs-CRP: High-sensitivity C-reactive protein
IRB: Institutional review board
KIOM: Korea Institute of Oriental Medicine
LDL-C: Low-density lipoprotein cholesterol
PCSK9: Proprotein convertase subtilisin/kexin type 9
PPS: Per protocol set
RCT: Randomized controlled trial
TC: Total cholesterol
TG: Triglyceride
TSH: Thyroid-stimulating hormone
